### Data management {19}

The data obtained in this study is collected and stored in compliance with the requirements of the General Data Protection Regulation of Germany (DSGVO). The data is collected using Unipark, a survey software that stores data encrypted on a German server; IP addresses are not stored in the log files. We will apply a key coding strategy for separating identified data from substantive data.

### Confidentiality {27}

The coding list is only accessible to the project leaders. It is stored on an encrypted local server at Philipps-Universität Marburg and deleted after completion of the data evaluation. The data will be treated strictly confidential.

### Plans for collection, laboratory evaluation, and storage of biological specimens for genetic or molecular analysis in this trial/future use {33}

n/a. No collection of biological specimens is required.

## Statistical methods

### Statistical methods for primary and secondary outcomes {20a}

Outcomes will be evaluated using intention-to-treat (ITT) analysis. Group differences (group: training group vs. waitlist control group) in primary (transcultural competence; MCI and OnTracc) and secondary outcomes (experiences in treating people from other cultures) will be examined using piecewise linear mixed-effects models with repeated measures (time point: pre, post, follow-up 1). Likely will piecewise linear mixed-effects models be used to examine the longer-term effect of the training (including the four time points: pre, post, follow-up 1, and follow-up 2). The significance level will be set at *p* < .05.

Sociodemographic data will be listed by group condition and for the total group. Group comparisons will be examined at baseline to check for successful randomization. Categorical data are reported as *N* (%), continuous data as mean (SD).

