It is expected that our study will increase transcultural competence in all three areas of transcultural competence [34, 35]: knowledge, skills, and awareness (primary outcomes). In addition, we expect that the training will increase treatment satisfaction and competence experienced when working with patients with diverse cultural backgrounds, as well as the number of patients with diverse cultural backgrounds treated (secondary outcomes). In the long term, the training is intended to be integrated into the continuing education of clinical psychologists.

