### Outcomes {12}

#### Primary outcome measures

The primary outcome is transcultural competence. Transcultural competence will be assessed at the beginning of the training, at the end of the training, and at the 2- and 6-month follow-up (see Fig. 1). For this purpose, the well-validated Multicultural Counseling Inventory (MCI) [44], translated into German by [name] [22], is used. The MCI captures general transcultural competence as conceptualized by Sue et al. [34]. With a total of 40 items, transcultural competence is assessed on the subscales *skills* (11 items, e.g., “I am able to quickly recognize and recover from cultural mistakes or misunderstandings.”), *cultural self-awareness and other-awareness* (10 items, e.g., “In order to be able to work with minority clients, I frequently seek consultation with multicultural experts and attend multicultural workshops or training sessions.”), and knowledge (11 items, e.g., “I use innovative concepts and treatment methods.”). In an additional fourth subscale, *therapeutic relationship* is assessed (8 items, e.g., “I am confident that my conceptualizations of client problems do not consist of stereotypes and biases.”). The MCI allows to compute both a total score and scores for the four subcategories. The 40 self-report items are answered on a 4-point Likert scale ranging from 1 (very inaccurate) to 4 (very accurate). Research indicates that the MCI is a suitable psychometrically robust instrument for evaluating transcultural competence in multicultural training processes [61]. The dimensions appeared to be distinct yet interrelated [61]. Internal consistency reliabilities (Cronbach’s alpha) ranged from .67 to .81 in the subscales and .86 for the full scale [44].

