**Fig. 1 Fig1:**
[figure not shown]
Schedule of enrolment, interventions, and assessments

A second questionnaire on transcultural competencies is included, which was specifically developed for the German psychotherapeutic setting, the OnTracc-questionnaire [45]. It contains 28-self-report statements, which are based on three factors, *engagement* (7 items, e.g., “I am actively involved in the process of reducing barriers for refugees and people with a migration background in accessing psychotherapy (e.g. against the shortage of translators).”), *awareness* (10 items, e.g., “I take cultural related differences in symptom description into account.”), and *challenges* (11 items, e.g., “I worry about my skills to work with refugees, because they have a different understanding of diseases and mind.”). The items are rated on a 5-point Likert scale from 1 (totally disagree) to 5 (totally agree). The OnTracc-questionnaire showed substantial convergent and discriminant validity to the MCI subscales and good reliability for all subscales (McDonald’s omega between .73 and .81) [45]. The OnTracc-questionnaire was likewise recommended for evaluating transcultural competence in training [45].

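### The protocol does not fix which score, which contrast and which success rule carry the primary claim, so the error rate of that claim is not controlled

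*Protocol article*

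**What the plan says.** The protocol describes the primary outcome at several levels.

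- **Outcomes {12}, Primary outcome measures:** one construct. "The primary outcome is transcultural competence. Transcultural competence will be assessed at the beginning of the training, at the end of the training" and at two follow-ups.
- **Background and rationale {6a}:** an expected increase in "all three areas of transcultural competence [34, 35]: knowledge, skills, and awareness (primary outcomes").
- **Objectives {7}, Participant timeline {13} and Statistical methods {20a}:** two instruments, the MCI and OnTracc. In {20a} the outcomes are "primary (transcultural competence; MCI and OnTracc) and secondary outcomes (experiences in treating people from other cultures").

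On scoring, "The MCI allows to compute both a total score and scores for the four subcategories". The fourth MCI subscale is therapeutic relationship. OnTracc has 28 statements, "which are based on three factors": engagement, awareness and challenges. No OnTracc total is described.

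Section {20a} specifies piecewise mixed models over pre, post and follow-up 1, and adds "The significance level will be set at *p* < .05". It does not say which score enters the model, which segment or contrast is confirmatory, or whether one or all results must be significant. Sample size {14} gives N = 174 for Glass' delta 0.5, alpha 0.05 and power 0.95, and ties this to no score.

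**The concern.** A reader cannot tell from the protocol which result would confirm efficacy. Following {20a} as written gives at least two primary tests, one per questionnaire, each at .05, while the sample size is set for one.

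The descriptions also do not reduce to one endpoint. The MCI total includes a subscale outside the three areas named in the Background. OnTracc measures neither knowledge nor skills as a factor. The sample item for the challenges factor is worded so that agreement means less confidence, so any combined OnTracc score would need a direction rule.

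The confirmatory result could therefore be chosen after the data are seen. That matters more here because the trial is unblinded {17a} and, as the Limitations say, rests on self-report alone. Dissemination plans {31a} and the Discussion make wider use of the training depend on the study succeeding, and success is not defined.

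**Working it through.** **Inputs from the protocol.** Alpha 0.05 ({14}, {20a}); delta 0.5, power 0.95, N = 174 ({14}); 1:1 allocation ({8}), so 87 per arm. Scores available: 5 from the MCI (total and four subscales) plus 3 OnTracc factors = 8.

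**Assumed.** Correlation between test statistics. The protocol reports that the instruments are related but gives no figure, so 0 to 0.9 is shown.

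**Step 1: the plan's own figure.** The two-mean formula is n per arm = 2(z_alpha + z_power)² / delta².
- One-sided: 2(1.645 + 1.645)² / 0.25 = 86.6, so 87 per arm and N = 174. This matches.
- Two-sided: 2(1.960 + 1.645)² / 0.25 = 103.96, so 104 per arm and N = 208. This does not match.
- A two-sided baseline-adjusted comparison multiplies n by (1 − r²) and also gives 174 if the pre–post correlation r is about 0.40 (assumed).

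The mixed-model calculation cannot be rerun because its variance and correlation inputs are not given. By every route that matches, 174 is the size for a single test at 0.05.

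**Step 2: error rate if any one significant score counts.** For independent tests the rate is 1 − 0.95^k: k = 2 gives 1 − 0.9025 = 9.75%, and k = 8 gives 1 − 0.6634 = 33.7%. For correlated tests, equicorrelated normal statistics were simulated (400,000 draws, two-sided cut-off 1.96).

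| Scores | corr. 0 | 0.3 | 0.5 | 0.7 | 0.9 |
|---|---|---|---|---|---|
| 2 | 9.75% | 9.5% | 9.1% | 8.4% | 7.0% |
| 3 | 14.3% | 13.7% | 12.6% | 10.9% | 8.3% |
| 8 | 33.7% | 30.0% | 25.1% | 19.0% | 11.9% |

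With one named score and contrast the rate is 5%. If all named scores must be significant, it is at most 5%.

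**Step 3: power with two primaries at 0.025 each, two-sided (critical value 2.241).**
- Accepting the stated 0.95: non-centrality 1.960 + 1.645 = 3.605, and 3.605 − 2.241 = 1.364, so power is 0.914.
- Simple two-sided two-mean check: non-centrality 0.5 × √(87/2) = 3.298. At 0.05, 3.298 − 1.960 = 1.338, so power is 0.910. At 0.025, 3.298 − 2.241 = 1.056, so power is 0.855.

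**Step 4: power if both must succeed.** Each test stays at 0.05, and joint power is at least 1 minus the two type II errors. This gives 1 − 0.05 − 0.05 = 0.90 from the stated power, or 1 − 0.09 − 0.09 = 0.82 from the simple check. Positive correlation would raise it.

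**The case against.** The wordings can be read as levels of one hierarchy: a construct, its components and its instruments. Objectives, Participant timeline and {20a} agree on the MCI and OnTracc, and the Background sentence is an expectation. That is fair, and the fault is more underspecification than three rival definitions. It does not remove the mismatch between OnTracc's factors and the three named areas, and it still leaves two primary instruments with no rule joining them.

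Two stronger readings are tempting, and the protocol supports neither.

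- **Eight scores are each tested at .05.** Section {20a} names only the two questionnaires. The sentence on MCI totals and subscales describes what the instrument can produce. Eight is the number available, not a stated number of tests.
- **The error rate is far above 5%.** This needs an any-of rule, which the protocol neither states nor excludes. An expected gain in all three areas could even be read as an all-of rule, which brings no inflation. For two related questionnaires the rate is at most 9.75%. The scores are described as interrelated and the MCI total contains its own subscales, so 33.7% is an upper figure for eight single tests.

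The rates also count results against the training. Counting only favourable results, two scores at correlation 0.5 give about 4.6%, but the single-test level to compare with is then 2.5%, so the relative inflation is similar. Choosing between the two model segments could add to the rates. No figure is put on that, because the protocol does not say that the later segment alone would count as efficacy.

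Finally, a multiplicity procedure may sit in an analysis plan that is not shown. The absence of an adjustment is therefore not the finding. The identity of the primary endpoint belongs in the protocol, which states in {31c} that it is complete, and there it is left open.

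**Conclusion.** The point holds as a failure to fix the primary score, contrast and success rule. The type I error of the primary claim depends on choices the protocol leaves open. It is 5% or less with one named score or an all-must-succeed rule. Under an any-of rule it is about 7–10% for the two questionnaires with one score each, and about 12–34% if all eight available scores were used. These ranges rest on two-sided tests at 0.05, one contrast per score, equal correlations between 0.9 and 0, and the any-of rule itself. The smaller range is the one closest to what {20a} says. Either way, the confirmatory result cannot be identified in advance from this document.

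**What to change.** Before data are analysed, choose one of the following.

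1. **One primary endpoint.** Name one score and one contrast, for example MCI total, group difference in change from t0 to t1, two-sided 0.05. Make the remaining MCI scores, the OnTracc factors and the 2-month contrast secondary.
2. **Two primary endpoints.** Name one MCI score and one OnTracc score, define the OnTracc score's direction, and name the contrast. Then either apply Holm over the two tests or state that both must be significant.

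Which score and time point lead is the sponsor's decision; what matters is that it is fixed. Then align the Background {6a}, Objectives {7}, Primary outcome measures {12}, Participant timeline {13} and Statistical methods {20a}.

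**Cost.** Recruitment began in April 2023, so this is an amendment. Section {25} requires ethics approval for changed outcomes, with an updated protocol and registry entry. Option 1 needs no alpha split, but {14} sized a three-time-point model, so the power for the chosen contrast should be confirmed. Under option 2 with Holm, power for either score at the 0.025 step is about 0.91 if the stated 0.95 is accepted, or about 0.85 by the simple two-sided check. Holm can only improve on this. With a both-must-succeed rule, joint power is at least 0.90 or 0.82 on the same two bases. In each case {14} should restate the power, with its sidedness and the score it refers to.

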#### Secondary outcome measures

In addition to transcultural competence, secondary outcomes serve to explore concrete experiences in treating patients with diverse cultural backgrounds. Eight items are used for this purpose. For example, the number of patients with diverse cultural backgrounds who are currently being treated by each participant in their clinical practice is recorded. The participants are further asked whether they are supervised in the field of transcultural therapy and whether they have ever worked with a language mediator. A 6-point Likert scale will additionally be used to assess satisfaction in therapies with patients with diverse cultural backgrounds and perceived competence. The items were taken from a preliminary study [62].

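### One linear mixed model is fixed for all secondary outcomes, although two appear to be yes/no items (one a lifetime item) and one is a count

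*Protocol article*

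**What the plan says.** The section on statistical methods for primary and secondary outcomes {20a} names the primary outcomes and the "secondary outcomes (experiences in treating people from other cultures") together. It says that group differences in them "will be examined using piecewise linear mixed-effects models with repeated measures" at pre, post and follow-up 1. The same type of model is foreseen for the four-time-point analysis.

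The section on secondary outcome measures says "Eight items are used for this purpose" and describes five of the eight:
- a count: "the number of patients with diverse cultural backgrounds who are currently being treated by each participant";
- an item on current status: "whether they are supervised in the field of transcultural therapy";
- a lifetime item: "whether they have ever worked with a language mediator";
- two ratings on a 6-point scale, for satisfaction and perceived competence.

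Section {18a} has the secondary outcomes collected at every time point, so the repeated-measures model applies to all of these items. Two other statements might seem to cover the yes/no items but do not. The logistic regression in {20b} is for adherence. The remark in {20a} that categorical data are shown as number and percentage is about description.

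**The concern.** The article chooses a model for the secondary outcomes, and the choice does not suit three of the five items it describes. This is therefore a stated method to correct, not a detail left to an analysis plan.

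A linear mixed model takes residual variance as constant. In its simplest form, with a random intercept only, it also takes the correlation between any two visits as equal. A 0/1 item whose yes answers can only accumulate breaks both assumptions. Its change from baseline grows more variable with each visit, while the model uses one standard error for every change. The test can then be too strict at one visit and too lenient at the next.

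For a patient count, variance usually rises with the mean, and a ratio is the natural summary. The count also carries a stated hypothesis: the end of the background section expects the number of such patients treated to rise.

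**Working it through.** **Inputs from the article.** N = 174 allocated 1:1 gives 174 / 2 = 87 per arm. The model is linear mixed, with visits at pre, post and follow-up 1. The significance level is 0.05.

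**Inputs assumed, since the article gives none.** Baseline yes p = 30% to 85%. New yes answers per interval among those still no: h = 5% or 10%. No training effect, complete data, random-intercept covariance. The article does not fix the covariance.

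**1. Who can still change on the lifetime item.** 174 × (1 − p) gives about 122, 87, 52 and 26 participants at p = 30%, 50%, 70% and 85%.

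**2. Why the error rate moves.** With q = 1 − p, the probabilities of a change are:
- pre to post: a = q·h
- post to follow-up 1: b = q·(1 − h)·h
- pre to follow-up 1: c = q·[1 − (1 − h)²]

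Each change is 0 or 1, so its variance is x(1 − x). With three balanced visits, the random-intercept model uses the mean of the three variances for every contrast. The actual rejection rate is then approximately 2·[1 − Φ(1.96 / √(true variance / mean variance))].

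Example with p = 50% and h = 10%:
- a = 0.0500, variance 0.0475
- b = 0.0450, variance 0.0430
- c = 0.0950, variance 0.0860
- mean variance = (0.0475 + 0.0430 + 0.0860) / 3 = 0.0588
- follow-up 1: ratio 0.0860 / 0.0588 = 1.46; 1.96 / √1.46 = 1.62; rejection about 10.5%
- post: ratio 0.0475 / 0.0588 = 0.81; 1.96 / √0.81 = 2.18; rejection about 2.9%

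**3. Simulation over the whole assumed range (87 per arm).** Rejection is about 8% to 12% at follow-up 1 and 1% to 3% at post. Single runs of 4,000 replicates reached 13% and 4%, which I read as simulation scatter. The lowest values come at 85% baseline yes with 5% new yes, where changes are too rare for the normal approximation.

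**4. The count.** The same linear model was applied to an overdispersed count with assumed mean 1, 3 or 6 and no effect. It rejects about 5% to 6% of the time. Type I error is close to nominal.

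**5. Not computed.** No error rate was derived for the supervision item, which can move in both directions.

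**The case against.** Several counter-arguments have force.

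- **The covariance is the cause, not linearity as such.** The article does not commit to a random intercept. Comparing changes from baseline with an unequal-variance t test, which is still a linear analysis, gives 2.3% to 4.9% rejection at follow-up 1 and 0.4% to 4.6% at post under the same assumptions. There is no inflation, only conservatism when changes are rare. This stands, and it limits the error-rate finding to the random-intercept form.
- **Caseload p values.** A reader might infer that p values and intervals for the patient count would be wrong. Step 4 of the check does not support that, and the article gives no caseload figures showing how small or skewed the counts are.
- **Impossible fitted values.** A reader might expect fitted proportions outside 0 to 1 or negative counts. With three visits, a knot at post and complete data, the piecewise group-by-time model reproduces the observed group means, which cannot leave the range. Only individual predictions could.
- **Noise and dilution.** A reader might infer that participants who answer yes at baseline only add noise. They contribute a change of exactly zero, so effect and variance shrink together. Suppose 60% answer yes at baseline: 0.40 × 87 = 35 per arm can change, and a 20-point rise among them is 0.40 × 20 = 8 points overall. That is mostly a change of denominator, and 8 points is the correct effect among all randomized. With assumed uptake of 5% versus 25% among the rest, power is about 60% in the full sample and 66% in the baseline-no subset.
- **Item format is inferred.** The article paraphrases the items. The yes/no format follows from their being asked as whether-questions, the recall window at follow-up is not stated, and three of the eight items are not described.
- **Weight.** The objectives section names the number of patients, satisfaction and competence as secondary. The supervision and mediator items appear only under the outcome measures, without a hypothesis.

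These points reduce the harm. They do not supply a suitable model for the three items, and no other part of the article does.

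**Conclusion.** The point holds in a limited form. The article fixes a linear mixed model for every secondary outcome, and that model fits the two apparently yes/no items and the patient count poorly.

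The measurable harm is on the lifetime language-mediator item. With a random-intercept model, a nominal 5% test runs at about 8% to 12% at follow-up 1 and 1% to 3% at post. This rests on the assumed baseline and uptake rates, on the random-intercept covariance, and on the item being a true lifetime yes/no question. For the count, the issue is fit and a less natural effect measure. All three items are secondary, so the primary conclusion on transcultural competence is untouched. The change is worth making because it is specific and cheap.

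**What to change.** Amend {20a} as follows:
- **Scale scores and 6-point ratings:** keep the piecewise linear mixed model, and limit it to these.
- **Yes/no items:** use a logistic mixed model, or GEE with robust errors, and report a risk difference and an odds ratio.
- **Language mediator:** analyse first use after randomization among those answering no at t0, up to follow-up 1, while the waitlist group is still untrained. The subset is defined before randomization, so the randomized comparison is preserved.
- **Patients currently treated:** use a negative-binomial model, or Poisson with robust errors, and report a rate ratio.

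The response format of all eight items should be stated so that each can be matched to its model.

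The cost is a change of analysis wording and standard software, with no new data. The small downside is in the mediator analysis: fewer participants, and a result that refers to those without earlier mediator use and not to everyone randomized. The report should state that denominator.

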### Interim analyses {21b}

n/a. Neither interim analyses nor formal stopping rules will be applied in our study, as this is not a clinical trial and poses low safety concerns.

### Methods for additional analyses (e.g., subgroup analyses) {20b}

Regarding additional analyses, we would like to examine the clinical psychologist’s socio-demographic influence on the outcomes (e.g., age, duration of activity as a therapist, own migration background, multilingualism, volunteering for refugees and patients from different countries). We will investigate socio-demographic variables and disparities, including an examination of potential differences in the dependent variable among the three German-speaking countries. Furthermore, a consistency test will be performed to compare the post-intervention effects between the training group and the waitlist control group. For this purpose, two models are computed, one with the group as a predictor and one without, and the two models are compared with each other. We also would like to examine the influence of adherence on the outcomes by means of completed modules by a logistic regression.

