### Trial design {8}

Our study is a two-armed, randomized-controlled trial (RCT) with two parallel groups (training group vs. waitlist control group) of equal size (1:1 ratio at randomization). The study is designed as a superiority trial investigating the efficacy of a 6-week transcultural competence training to improve transcultural competence in clinical psychologists as compared to a waitlist control group. Furthermore, potential mediators and moderators of the training effect will be investigated in the trial.

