### Participant timeline {13}

Via a link, participants can access the detailed description and the inclusion criteria of the study online. After accepting the informed consent, the participants will be forwarded to the pre-training assessment (t0). During the pre-training assessment, the control variables as well as the primary (Multicultural Counseling Inventory and OnTracc) and secondary outcomes are measured. The participants will subsequently be randomized. The TG will directly start with the training. After the training (t1) and 2 (t4) and 6 months later (t5), the assessments are carried out again. The WG will complete a control assessment (t1) after the training group has completed the training. They will also complete the 2-month follow-up assessment (t2). After the 2-month follow-up assessment, they will start the training. After the training (t3) and 2 (t4) and 6 months (t5) later, they will complete the assessments. For the participant timeline, please refer to Fig. 1.

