### Sample size {14}

To the authors' knowledge, there are no web-based training programs for transcultural competence in Germany. For this reason, a concise estimate of the expected effect size is difficult to provide. A systematic review from 2020 on the effectiveness of cultural competence with nine studies showed effect sizes from small (*d* = 0.10) to large (*d* = 2.11) [63]. An online intervention to increase transcultural competence in the USA revealed medium effect sizes for the dimension attitudes and skills and large effect sizes for the dimension knowledge [40]. Based on the mixed results, we opted for a medium effect size.

A calculation with the Shiny App [64] with an effect size of *Glass’ delta* = 0.5 showed that a linear mixed model 3 (measurement time: pre, post, follow-up 1) × 2 (groups: training group vs. waitlist control group) requires a sample number of *N* = 174 (*α* = 0.05, power = 0.95).

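### The consistency test is meant to compare training effects, but read literally it compares score levels, and without an interval it cannot support a claim of consistency

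*Protocol article*

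**What the plan says.** The section on additional analyses {20b} of the protocol article gives an aim and a method. The aim: "a consistency test will be performed to compare the post-intervention effects between the training group and the waitlist control group". The method: "two models are computed, one with the group as a predictor and one without, and the two models are compared with each other". It does not say whether group enters alone or together with its time terms, which visits are used, or which result would count as consistent.

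The participant timeline {13} places the waitlist arm's training late. This arm completes t0, t1 and t2, and "After the 2-month follow-up assessment, they will start the training"; its post-training assessment is t3. The training group starts after t0 and has its post-training assessment at t1.

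The only general decision rule is in the statistical methods {20a}: "The significance level will be set at *p* < .05". The trial is described as a superiority design, and no equivalence margin appears anywhere.

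**The concern.** Whether the training works equally well in both arms is a question about change: does the gain from before to after training differ between arms? In a repeated-measures model the group-by-time term answers it. Adding or removing group as a predictor, taken at its word, asks whether scores differ in level. The two answers can part company in both directions. A real difference in gains can be diluted, and a level difference that predates training can look like a difference in effect.

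The design gives such a level difference room to arise. Randomisation balances the arms at t0 on average, but the waitlist arm reaches its training after a waiting period and three rounds of self-report questionnaires. Any drift or selective dropout before t2 is part of its level when training begins.

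The label of the test also invites a conclusion that a model comparison at the 5% level cannot deliver. At stake is whether a later report may say that the waitlist arm replicated the training effect.

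**Working it through.** **Plan's own figure.** No figure is given for the consistency test. The number per arm comes from the sample size section {14}: "we opted for a medium effect size" (Glass' delta 0.5), and the model "requires a sample number of *N* = 174 (*α* = 0.05, power = 0.95". With arms "of equal size (1:1 ratio at randomization", that is 174 / 2 = 87 per arm. A plain two-mean formula with one-sided alpha 0.05 gives 2 × (1.645 + 1.645)² / 0.5² = 86.6, so 87 per arm and N = 174. A two-sided test at one time point would need 104 per arm, and a two-sided ANCOVA with an assumed baseline correlation of 0.4 gives N = 176. The article states neither sidedness nor correlation, so 174 is not in dispute. It is used here only as the available number.

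**Assumptions (not in the article).** SD 1 at each visit, pre-post correlation r of 0.5 to 0.7, two-sided 5% tests, and 70 per arm contributing as an illustration of dropout (70 / 87 = 80%).

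**Step 1: level against change.** Let gains be 0.5 and 0.25 SD from equal starting levels, with n = 87 and r = 0.5.

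- Averaged over pre and post, the arms differ by 0.25 / 2 = 0.125 SD. SE = sqrt((1 + r)/2 × 2/n) = sqrt(0.75 × 2/87) = 0.131. Ratio 0.95, power about 16%.
- In change, the arms differ by 0.25 SD. SE = sqrt(2(1 − r) × 2/n) = sqrt(2/87) = 0.152. Ratio 1.65, power about 38%.

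A simulation of 4,000 runs per scenario under the same assumptions gave these rejection rates:

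| Scenario (training group, waitlist) | Group main effect | Post-training level only | Group-by-time (change) |
|---|---|---|---|
| Gains 0.5 and 0.25, equal start | 16% | 38% | 38% |
| Gains 0.5 and 0.5, waitlist starts 0.3 higher | 61% | 50% | 5% |
| Gains 0.5 and 0, waitlist starts 0.25 higher | 5% | 39% | 90% |
| Gains 0.5 and 0.25, waitlist starts 0.25 higher | 15% | 5% | 37% |

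The first row needs no imbalance, and the main effect still dilutes the difference. The other rows show what a shift before training does to either form of level test. The change test is unaffected by it.

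**Step 2: what the right contrast can show.** SE of the difference in change = sqrt(2(1 − r) × 2/n), with r = 0.6.

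- n = 70: sqrt(0.8 × 2/70) = 0.151; 95% half-width 1.96 × 0.151 = 0.30 SD.
- n = 87: sqrt(0.8 × 2/87) = 0.136; 95% half-width 1.96 × 0.136 = 0.27 SD.

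A true difference of 0.25 SD, half the planned effect, would then be non-significant 62% of the time (n = 70) or 55% (n = 87). At 87 per arm, power for that difference runs from 38% (r = 0.5) to 57% (r = 0.7). Even an observed difference of zero would leave an interval of about ±0.27 SD or wider at r = 0.6, so differences of 0.25 SD would not be excluded.

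**The case against.** The strongest reply is that the article writes in shorthand. Its framework is piecewise mixed models with repeated measures, and its primary analysis too is described as group differences without spelling out an interaction. A model with group may therefore add group together with its time terms, and the stated aim speaks of effects. This stands: a reader might infer that only a group main effect will be fitted, but that is the literal reading and not an explicit statement.

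A reader might also infer that a non-significant comparison will be taken as proof of consistency. The article gives no such rule. What can be said is narrower: the test as described offers no other basis for a consistency conclusion.

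Three further points hold.

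- The different starting visits of the two arms are a feature of the waitlist design, not an error, and the proposed fix keeps them. What is missing is the naming of each arm's reference visit.
- The 62% and 55% miss rates describe sample size. They would be the same after the fix and do not measure the cost of the wrong contrast.
- The larger divergences in the table need assumed shifts of 0.25 to 0.3 SD. As chance imbalances at t0 these would be about 1.6 to 2.0 standard errors (0.25 and 0.3 over 0.152), and nothing in the article quantifies drift during waiting.

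Model terms for an additional analysis may also sit in an analysis plan not shown here. That does not remove the point, because the article does state a method, and the method as worded does not match the aim stated in the sentence before it.

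**Conclusion.** The concern holds in limited form. The stated comparison, read literally, tests levels where the aim is to compare training effects. In a pre-post model this cuts power for a 0.25 SD difference in gains from about 38% to 16% (87 per arm, r = 0.5 assumed), and it lets drift in the waitlist arm before t2 count as a difference in effect. If group is meant to include its time interaction, the contrast is right, but a bare model comparison at the 5% level still cannot support a claim of consistency: the 95% half-width is about 0.27 to 0.30 SD for 87 to 70 per arm (r = 0.6 assumed). All these sizes rest on assumed correlations and, for 70 per arm, on assumed dropout. Severity is low, since this is one additional analysis and neither the primary comparison nor the sample size depends on it.

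**What to change.** Replace the comparison of models with and without group by an estimate. For each arm, take the change across its own training period: t0 to t1 in the training group, t2 to t3 in the waitlist arm. Report the between-arm difference in change (the group-by-time term) with a 95% CI, and state that a non-significant comparison alone will not be reported as consistency.

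This changes wording only; all four assessments are already scheduled. The downside is that the interval will probably be too wide for a strong statement. If the authors do want to claim consistency, they would need a margin fixed in advance. With two one-sided 5% tests, 80% power and r from 0.7 to 0.5, a margin of 0.25 SD would need 165 to 275 per arm against 87 randomised. A margin of 0.5 SD would need only 42 to 69, but it is as large as the planned effect itself.
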